#### Definitions of outcomes.

The primary outcome is defined as the incidence of ischemic stroke during the 6-month follow-up period after surgery. This outcome will be assessed based on clinical evaluation and confirmed by neuroimaging (MRI or CT) in cases of suspected new neurological deficits, in accordance with standard diagnostic criteria for ischemic stroke.

Secondary outcomes included early postoperative haemodynamic change (≤7 days) assessed using the same imaging modality; graft patency was defined as uninterrupted flow through the bypass on intraoperative ICG and postoperative CTA; changes in cerebral haemodynamic status from baseline to 6 months after surgery will be assessed using ASL MRI and defined as a quantitative increase in regional CBF in the affected hemisphere and/or a reduction in interhemispheric perfusion asymmetry compared with baseline; change in neurological status from baseline to 6 months assessed using the NIHSS and the mRS; changes in cognitive function from baseline to 6 months based on standardised neuropsychological testing; all-cause mortality at 6 months; perioperative complications within 30 days (including intracranial haemorrhage, hyperperfusion syndrome, seizures, wound complications, and graft occlusion); and angiographic extent of revascularisation on follow-up imaging.

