### Statistical analysis

Continuous variables will be reported as mean with standard deviation or median with interquartile range, depending on distribution. Categorical variables will be presented as frequencies and percentages. The primary outcome, change in cerebral hemodynamic status from baseline to 6 months, will be analyzed using a paired t-test or Wilcoxon signed-rank test, depending on data distribution. Mean change in CBF and/or perfusion asymmetry will be reported with 95% confidence intervals.

Early postoperative and 6-month changes in neurological and cognitive scores will be analyzed using paired tests. Categorical outcomes, including graft patency, recurrent TIA or stroke, complications, and mortality, will be reported as proportions with 95% confidence intervals.

Where appropriate, exploratory regression analyses will be performed to identify factors associated with hemodynamic improvement and clinical outcomes. Potential predictors may include age, sex, baseline perfusion deficit, vascular risk factors, duration of symptoms, and preoperative neurological status. Given the limited sample size, multivariable models will be restricted to a small number of clinically relevant covariates.

Because repeated measurements will be obtained from the same participants, analyses will account for within-subject correlation. Continuous repeated outcomes will be analysed using linear mixed-effects models, with time point entered as a fixed effect and participant ID as a random intercept. This approach allows estimation of postoperative change while accounting for correlation between repeated measures within individuals and accommodating incomplete follow-up data under a missing-at-random assumption.

A p-value <0.05 will be considered statistically significant. All analysis will be performed using Stata 19.5.

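### The six-month hemodynamic change has two measures joined by 'and/or' and two competing analyses, and the three-visit random-intercept model can misstate its standard error

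*Protocol article*

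**What the plan says.** Two places define the measure. The Definitions of outcomes section lists the six-month hemodynamic change among the secondary outcomes and describes it as a "quantitative increase in regional CBF in the affected hemisphere and/or a reduction in interhemispheric perfusion asymmetry compared with baseline". The Statistical analysis section calls the same quantity primary and keeps the alternative open: "Mean change in CBF and/or perfusion asymmetry will be reported with 95% confidence intervals".

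Two kinds of analysis are assigned to it. The hemodynamic outcome "will be analyzed using a paired t-test or Wilcoxon signed-rank test, depending on data distribution". Three paragraphs later, "Continuous repeated outcomes will be analysed using linear mixed-effects models", "with time point entered as a fixed effect and participant ID as a random intercept". Missing data handling again assigns mixed models to longitudinal analyses. Table 1 schedules ASL perfusion metrics and CBF asymmetry indices at Preop, PostOp0 and PostOp6, so the mixed model covers the same outcome.

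All tests use p<0.05. The text states no order between measures or analyses, no multiplicity rule, no criterion for choosing between the two paired tests, and no residual covariance, random slope or robust standard error beyond the random intercept.

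**The concern.** The sample size section describes one paired comparison at one two-sided 0.05. The analysis text does not match this: two measures could each carry the result, and each could be analysed in two ways. A reader of the final report could not tell whether the measure and method shown were the ones intended from the start.

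The mixed model raises a further question. With three visits, a random intercept as the only source of within-patient correlation forces the same variance at every visit and the same correlation between every pair. The visits are before surgery, 3–5 days after it, and six months after it. The spacing is very unequal, and an operation falls between the first two. If variances or correlations differ, the model pools the wrong information into the standard error of the six-month contrast, and the confidence interval and p-value are off in a direction that cannot be known in advance.

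**Working it through.** **1. The plan's own figures.** Inputs from Sample size calculation: effect size 0.40, within-subject correlation ρ = 0.5, two-sided α = 0.05, paired t-test. The SD of the change is SD·√(2(1−ρ)), which equals the SD at ρ = 0.5, so the standardised change is 0.40. The noncentral t gives power 0.79992 at n = 51 and 0.808 at n = 52, so 52 is right. At n = 60 the power is 0.862. With ρ = 0.3 the standardised change is 0.40/√1.4 = 0.338 and power is 0.731. With ρ = 0.7 it is 0.40/√0.6 = 0.516 and power is 0.976. The stated 52, 86% and 73–98% all reproduce. They describe one measure and one paired test.

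**2. Two measures, each at 0.05.** If the two changes are independent, the chance of at least one false positive is 1 − 0.95² = 9.75%. Simulation with n = 60 and no true change gives about 8.4% at correlation 0.7 and 6.6% at 0.9. The protocol gives no correlation between the two measures, so the range is about 7–10%.

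**3. Random intercept with three visits.** With complete data, the model's standard error for any contrast between visits is √(2·MSE/n), where MSE has expectation (mean variance − mean covariance). The true variance of the six-month change is Var(pre) + Var(6m) − 2·Cov(pre, 6m). So

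model SE / true SE = √[2(mean variance − mean covariance)] / SD(six-month change).

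Example with correlations pre–early 0.7, pre–6m 0.3, early–6m 0.5 and equal variances: the mean covariance is 0.5, the numerator is √(2 × 0.5) = 1, the denominator is √(2 × 0.7) = 1.183, and the ratio is 0.845.

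Example with an early-visit SD 1.5 times the others and all correlations 0.5: the mean variance is (1 + 2.25 + 1)/3 = 1.417, the mean covariance is (0.75 + 0.5 + 0.75)/3 = 0.667, the numerator is √1.5 = 1.225, the denominator is 1, and the ratio is 1.225.

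Rejection under no true change, n = 60, 20,000 simulated trials per row. The covariances are assumptions.

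| pre–early / pre–6m / early–6m | SE ratio | rejection at nominal 5% |
|---|---|---|
| 0.5 / 0.5 / 0.5 | 1.00 | 5.3% |
| 0.7 / 0.5 / 0.5 | 0.93 | 7.2% |
| 0.7 / 0.5 / 0.6 | 0.89 | 8.0% |
| 0.7 / 0.3 / 0.5 | 0.85 | 10.2% |
| 0.9 / 0.5 / 0.6 | 0.82 | 11.0% |
| 0.3 / 0.5 / 0.3 | 1.13 | 3.0% |
| all 0.5, early SD × 1.5 | 1.22 | 1.8% |

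A more extreme pattern, 0.3 / 0.7 / 0.3, takes rejection down to 0.8% (ratio 1.37). The paired t-test stays close to 5% in every row.

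**4. Only two visits in the model.** In one simulated data set of 60 patients, the random-intercept standard error for the six-month change was 0.1246 with three visits. With baseline and month 6 only it was 0.1288, the same as the paired standard error. The problem therefore enters with the early visit.

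**The case against.** Much of the opposing case is sound.

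- **Standard errors.** A reader might infer that the random-intercept model gives wrong standard errors here. The documents do not support that. They state a single within-subject correlation of 0.5 with a range of 0.3–0.7, and no visit-specific SDs. Under compound symmetry the model is correct. Nor is the direction known: scans a few days apart might be expected to correlate more, but surgery lies between them and could lower that correlation. One row of the table (0.9) also lies outside the protocol's range.
- **Number of tests.** The t-test and signed-rank test are one conditional choice, so the unresolved conflict is between a paired test and a mixed model. The paired test is the one named for this outcome, but the mixed-model sentence covers it too and neither is given precedence.
- **Incomplete patients.** One might say that the paired test uses completers only, or that the mixed model alone keeps patients with missing visits. Missing data handling also allows multiple imputation, so neither follows.
- **Any improvement at all.** One might count how often an unchanged patient shows some rise in CBF or some fall in asymmetry by chance: 75% if the measures are independent, 57% at correlation 0.9. No responder proportion is planned. The stated analysis compares means or ranks, so this figure does not measure an error in it.
- **Unseen SAP and status of the outcome.** Degrees-of-freedom methods and normality criteria may properly sit in an SAP. The and/or, the two analyses and the random intercept are, however, written into this text. The outcome is primary in one section and secondary in another. If it is secondary, the stakes are lower, but the result still cannot be tied to one prespecified measure and method.

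**Conclusion.** The point holds in a limited form. It is certain from the text that two measures are joined by and/or, that a paired test and a mixed model are both assigned to the outcome, and that no hierarchy or multiplicity rule is stated. The 7–10% false-positive rate assumes that both measures are tested at 0.05, that either may count, and that their changes correlate between 0.9 and 0.

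The standard-error point is a risk, not a demonstrated error. The random-intercept model can be anti-conservative or conservative for the six-month contrast, with rejection of about 2–11% in the tabulated settings, all resting on assumed covariances. The sample size figures reproduce and are not in question. The change should be made because it is cheap and the analysis text can still be fixed before results are seen.

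**What to change.** 1. Replace and/or in both sections with one named decisive measure, and label the other supportive.
2. Name one decisive analysis: a repeated-measures model with categorical time (Preop, PostOp0, PostOp6), unstructured residual covariance, REML and Kenward–Roger degrees of freedom, reporting the month-6 minus baseline contrast with a 95% confidence interval. Stata's mixed command can fit this. Keep the paired t-test or signed-rank test as a sensitivity analysis.
3. If asymmetry is the decisive measure, deal with its use for eligibility. Patients enter on an ASL deficit of at least 30% against the other hemisphere, and there is no control arm, so part of any fall may be regression to the mean. For a normal measure with no true change, the expected fall in SD units is (1 − ρ)·φ(c)/f, where f is the assumed fraction of screened patients who pass and c the matching cut-off. With f = 0.5 and ρ = 0.5 this is 0.5 × 0.798 = 0.40 SD. In simulation with n = 60, ρ of 0.5–0.7 and f from 84% down to 50%, a paired test rejects in about 15% to 91% of trials. All of these inputs are assumptions. Either use a baseline scan separate from the eligibility scan where one exists, or state this limit on the conclusion.

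Cost: a few sentences, and six covariance parameters in place of two, which is manageable with 60 patients. The target of 60 does not change.

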#### Mortality analysis.

All-cause mortality will be assessed 6 months after surgery. Mortality will be reported as the number and proportion of deaths with exact 95% confidence intervals.

Time-to-event analysis will be performed using Kaplan-Meier survival curves, with survival probability reported for the follow-up period. Patients alive at the last follow-up will be censored on the date of last clinical contact. Considering the cohort of 60 patients, Cox regression will not be performed unless the number of events is sufficient.

#### Missing data handling.

Missing data will be evaluated for extent and pattern. Longitudinal analyses will use mixed-effects models, which account for within-subject correlation and allow inclusion of incomplete observations under a missing-at-random assumption. Where appropriate, multiple imputations by chained equations will be used, with sensitivity analyses performed to assess robustness. For time-to-event outcomes, patients will be censored at the last follow-up.

### Ethics

Prior to registration, all participants will provide written informed permission in compliance of the Declaration of Helsinki’s ethical guidelines.

Patient confidentiality will be ensured through strict coding and anonymization of personal identifiers and medical record identification numbers (MRINs).

Institutional Review Board Statement: The study will adhere strictly to scientific ethics principles, including prevention of data fabrication, falsification, plagiarism, and false authorship. The study protocol and other necessary documents were reviewed and approved by the ethics committee (Protocol No. 4 of September 25, 2024, S2 Appendix). This study was retrospectively registered on ClinicalTrials.gov (NCT07396025; February 5, 2026) due to an administrative delay that prevented registration before participant enrolment; however, the study protocol, eligibility criteria, intervention, and outcome measures were predefined prior to recruitment and remained unchanged after registration. This study will be conducted according to the principles of the Declaration of Helsinki and subsequent amendments.

Informed Consent Statement: Written informed consent has been obtained from the patient(s) to publish this paper.

The authors confirm that all ongoing and related trials for this drug/intervention are registered.

## Discussion

This prospective single-arm interventional cohort study is designed to evaluate hemodynamic, neurological, and cognitive outcomes following STA-MCA bypass in patients with chronic ICA occlusion and documented cerebral hypoperfusion. Despite advances in evidence-based medical management, recurrent ischemic events remain common in selected patients with large-vessel cerebrovascular disease, particularly among those with persistent hemodynamic compromise [22,23]. Although EC–IC bypass remains controversial, accumulating evidence suggests that surgical revascularization may still represent a therapeutic option for carefully selected high-risk patients with recurrent ischemic symptoms despite optimized medical therapy [24,25].

A major challenge in chronic carotid artery occlusive disease is understanding the relationship between postoperative hemodynamic improvement and functional recovery. Previous studies of EC-IC bypass have largely focused on recurrent stroke prevention, graft patency, and perioperative safety, while substantially less attention has been directed toward postoperative neurological and cognitive trajectories [25]. This gap in evidence is particularly important because restoration of CBF may influence not only recurrent ischemic risk but also neurological recovery and cognitive function, outcomes that remain insufficiently characterized in patients with chronic ICA occlusion.

To address this limitation, the present study incorporates a multidimensional postoperative assessment integrating neuroradiological, hemodynamic, neurological, and neuropsychological measures. Specifically, repeated ASL MRI will be used to quantify cerebral perfusion changes after surgery, while angiographic assessment will characterize collateral circulation and donor vessel adaptation. These measures will be correlated with longitudinal changes in neurological and cognitive function to determine whether postoperative hemodynamic improvement translates into clinically meaningful recovery.

The use of ASL perfusion imaging represents an important strength of this protocol. Unlike contrast-enhanced techniques, ASL permits quantitative, non-invasive assessment of CBF without exogenous tracers, facilitating repeated longitudinal measurements after revascularization [26–28]. Although ASL has demonstrated value in predicting postoperative hemodynamic improvement after revascularization in conditions such as moyamoya disease, evidence in chronic ICA occlusion remains limited [26,27]. By incorporating serial perfusion imaging, the present study may improve understanding of the temporal relationship between cerebral perfusion restoration and postoperative recovery.

Existing studies investigating cognitive outcomes following EC–IC bypass remain limited by small sample sizes, heterogeneous methodologies, and incomplete follow-up. The Randomized Evaluation of Carotid Occlusion and Neurocognition (RECON) study, an ancillary investigation of the COSS trial, found no significant differences in cognitive outcomes between surgical and medical treatment groups; however, interpretation was limited by premature trial termination and a small sample size [29]. Similar limitations were reported in another prospective study, in which only a small proportion of screened patients completed longitudinal neuropsychological assessment [30]. More recently, Yu Duan et al. demonstrated that postoperative cerebral perfusion improvement following EC-IC bypass in elderly patients with chronic middle cerebral artery occlusion was associated with improved cognitive function [32]. Nevertheless, the study was restricted to middle cerebral artery disease and primarily relied on the MoCA, which may not adequately capture domain-specific cognitive changes following revascularization.

In our study the MoCA will be used as a global cognitive screening instrument because of its established sensitivity for detecting mild cognitive impairment and executive dysfunction, particularly in patients with vascular cognitive impairment [18]. However, as a screening tool, the MoCA alone may insufficiently characterize subtle domain-specific postoperative cognitive changes, particularly single-domain impairments [23]. Therefore, additional neuropsychological tests were incorporated to assess cognitive domains potentially affected by chronic cerebral hypoperfusion and altered cerebral hemodynamics.

The RAVLT was selected to assess verbal learning and memory processes, including immediate recall, delayed recall, and recognition memory, which may be sensitive to functional changes in cerebral perfusion and network connectivity [24]. Previous studies have demonstrated the utility of the RAVLT in detecting subtle memory dysfunction and in functional neuroimaging paradigms evaluating verbal memory processing [25]. In addition, the test has been validated across different populations and age groups, supporting its applicability in longitudinal cognitive assessment [31].

The Kohs Block Design Test was included to assess visuospatial abilities, perceptual organization, and nonverbal executive functioning, domains commonly affected in cerebrovascular disease and widely evaluated through constructional praxis and block design paradigms in neuropsychological assessment [26]. The test reflects visuospatial constructional ability and nonverbal problem-solving skills, which are important determinants of functional independence in activities of daily living, including post-stroke recovery [27].

The Stroop Color and Word Test was used to assess executive function, particularly inhibitory control and selective attention, which are commonly impaired after stroke. Its proven reliability, validity, and responsiveness in stroke populations further support its suitability for detecting and monitoring cognitive dysfunction in this setting [21,28,29].

Intraoperative assessment of cerebral hemodynamics represents another understudied aspect of revascularization surgery. ICG fluorescence angiography has demonstrated utility in assessing intraoperative perfusion and predicting complications such as cerebral hyperperfusion syndrome [30]. However, the relationship between postoperative graft adaptation, changes in STA caliber, cerebral perfusion improvement, and subsequent neurological or cognitive recovery has not been systematically investigated. The present study seeks to address this gap through combined angiographic and perfusion-based assessment.

Importantly, this study is not designed to evaluate the comparative efficacy or effectiveness of EC-IC bypass relative to conservative treatment, as no control group is included. Rather, the objective is to characterize recurrent cerebrovascular events, postoperative hemodynamic changes, and neurological and cognitive trajectories following STA-MCA bypass in a carefully selected cohort of patients with chronic ICA occlusion and documented cerebral hypoperfusion. This approach is intended to generate clinically meaningful evidence regarding recovery patterns and prognostic indicators that may inform future comparative studies and improve patient selection for surgical revascularization.

Overall, by integrating recurrent ischemic outcomes with perfusional, neurological, and neurocognitive assessments, the present study aims to improve understanding of the functional consequences of cerebral revascularization in chronic carotid artery occlusive disease. Better characterization of the relationship between cerebral perfusion restoration and clinical recovery may support more individualized surgical decision-making and improve prognostic assessment in patients undergoing STA-MCA bypass.

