To address these knowledge gaps, this prospective single-arm interventional cohort study aims to evaluate hemodynamic, neurological, and cognitive outcomes following STA-MCA bypass in patients with chronic ICA occlusion and documented cerebral hypoperfusion. The primary endpoint is the incidence of recurrent ischemic cerebrovascular events, defined as ischemic stroke or transient ischemic attack occurring within 6 months after surgery. The secondary endpoints include postoperative neurological and cognitive improvement, assessed using standardized neurological and neuropsychological measures, and their relationship with changes in cerebral perfusion assessed using arterial spin labeling magnetic resonance imaging and angiographic parameters of revascularization. Specifically, the study aims to investigate whether postoperative hemodynamic improvement correlates with neurological recovery and cognitive trajectories following revascularization. By integrating radiological, perfusional, and functional assessments, this study seeks to improve prognostic evaluation and refine patient selection for surgical revascularization in chronic carotid artery occlusive disease.

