### Data management

The collected data will be meticulously entered into a database, where revascularisation progress, the development of collateral circulation, and perfusion changes correlated with neurological and cognitive shifts will be evaluated. All data will undergo statistical processing and analysis to identify patterns and correlations, as well as survival analysis to assess collateral development and psychoneurological dynamics. All participants are expected to complete study visits over the planned 6-month follow-up period.

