### Limitations

This study has several limitations. First, its single-center, open-label design may limit the generalizability of the findings and introduces a potential risk of selection bias. However, conducting the study in a high-volume tertiary neurosurgical center ensures consistency in surgical technique, perioperative management, and imaging protocols.

Second, the absence of a non-surgical control group precludes direct comparison between surgical revascularisation and best medical therapy. Nevertheless, the primary objective of this study is not to reassess the efficacy of STA-MCA bypass versus conservative treatment, but rather to investigate detailed hemodynamic, neurological, and cognitive changes following bypass surgery in a carefully selected population with documented cerebral hypoperfusion.

Third, the planned sample size of 60 participants was primarily determined based on feasibility considerations, including the recruitment capacity of our center, the predefined study duration, and the scope of the funded grant project. As a result, the planned sample size may limit statistical power for detecting small effect sizes and for building robust predictive models. Therefore, multivariable analyses will be considered exploratory, and results will be interpreted cautiously. Larger multicenter studies will be required to externally validate the findings.

Fourth, the single-arm study design without a control group limits the ability to control for confounding factors and precludes definitive causal inference regarding the observed effects. As a result, the findings should be interpreted as associative, and residual confounding cannot be excluded despite adjustment in exploratory analyses.

Fifth, cognitive assessment may be influenced by learning effects, mood, fatigue, or educational background. To mitigate these factors, standardized testing conditions will be applied, parallel test versions will be used when available, and cognitive reserve indicators will be incorporated into the analysis.

Sixth, advanced imaging techniques such as ASL MRI and intraoperative ICG FLOW800 analysis require specialized equipment and expertise, which may limit reproducibility in lower-resource settings. However, these techniques provide unique insights into cerebral hemodynamics and represent a major strength of the study.

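### The Discussion says the perfusion–recovery correlations will settle whether haemodynamic gain becomes recovery, but the article ranks none of at least 12 to 16 pairs and does not label them exploratory

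*Protocol article*

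**What the plan says.** The Introduction lists the relationship between perfusion change and recovery among the secondary endpoints and adds: "Specifically, the study aims to investigate whether postoperative hemodynamic improvement correlates with neurological recovery and cognitive trajectories following revascularization". The Discussion words the same aim more strongly: "These measures will be correlated with longitudinal changes in neurological and cognitive function to determine whether postoperative hemodynamic improvement translates into clinically meaningful recovery".

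The ingredients are spread over several sections:

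- **Perfusion.** Definitions of outcomes describes haemodynamic change as "a quantitative increase in regional CBF in the affected hemisphere and/or a reduction in interhemispheric perfusion asymmetry compared with baseline". These are two measures, joined without priority.
- **Scores.** Follow-up assessment lists six instruments: NIHSS, mRS, MoCA, RAVLT, Kohs Block Design and Stroop. Cognitive function assessment splits the RAVLT into three sub-scores.
- **Intervals.** Statistical analysis refers to both early postoperative and 6-month changes in the scores.
- **Angiography.** The Discussion includes collateral circulation and donor-vessel adaptation among the measures to be correlated.
- **Scope.** Data management says: "All data will undergo statistical processing and analysis to identify patterns and correlations".
- **Threshold.** Statistical analysis says: "A p-value <0.05 will be considered statistically significant". It states no multiplicity rule.

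Statistical analysis calls its predictor regressions exploratory. Limitations says: "Therefore, multivariable analyses will be considered exploratory, and results will be interpreted cautiously". It also describes the findings as associative and says larger multicentre studies are needed to validate them externally.

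**The concern.** A sentence that promises to settle a question needs a rule for what would settle it. Here several perfusion measures can be paired with many scores, each pair can be declared significant at 0.05, and no pair is marked as the one that counts. A chance correlation could then be reported as showing that better perfusion becomes functional recovery. Conversely, a null result on the pair that matters most could be overshadowed by another pair that happens to cross the threshold.

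The article says its results may refine surgical decision-making and patient selection, so readers may give such a correlation weight. The labels that would normally guard against this are attached to other analyses.

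**Working it through.** **The plan's own figure.** The article gives no error rate for the correlations. Its only quantitative planning is the paired-means sample size. With the effect of 0.40 standardised by the single-occasion SD, the paired effect is d = 0.40/√(2(1 − ρ)).

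- ρ = 0.5: d = 0.40. The exact noncentral-t calculation requires 52 patients (power 80.8%), and 60 patients give 86.2%.
- 60 patients, ρ = 0.3: 73.1%.
- 60 patients, ρ = 0.7: 97.6%.

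These match the stated 52, about 86%, and 73% to 98%. They concern pre–post change, so they say nothing about the correlations, but they supply the patient numbers used below.

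**Counting the pairs at one interval.**

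- 2 perfusion measures × 6 instruments = 12.
- Counting three RAVLT sub-scores in place of one gives 6 − 1 + 3 = 8 scores, and 2 × 8 = 16.
- Using both intervals doubles this to 24 to 32. Angiographic measures add more, but the article does not fix their number.

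**Chance of at least one false p < 0.05, independent tests.** The formula is 1 − 0.95^k.

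- k = 12: 1 − 0.95^12 = 46.0%.
- k = 16: 1 − 0.95^16 = 56.0%.
- k = 24 and k = 32 (both intervals): 70.8% and 80.6%.

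**Correlated tests.** Perfusion measures will be related to each other, and so will the scores, which lowers these figures. The document gives no correlations, so the values below are assumptions. All perfusion-by-score Pearson correlations were simulated with no true association, 20,000 runs per setting, two-sided 0.05. The critical |r| at 60 patients is 0.254.

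| Assumed correlation between perfusion measures | Assumed correlation between scores | 12 pairs, n = 60 | 16 pairs, n = 60 |
|---|---|---|---|
| 0.5 | 0.3 | 39.6% | 48.4% |
| 0.8 | 0.3 | 35.8% | 43.6% |
| 0.8 | 0.5 | 30.9% | 37.1% |
| 0.8 | 0.7 | 24.6% | 28.0% |
| 0.9 | 0.8 | 18.9% | 21.6% |

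At 52 patients the results are nearly the same. For the 0.5/0.3, 0.8/0.5 and 0.8/0.7 settings they are 40.4%, 30.9% and 24.9% with 12 pairs, and 48.8%, 36.8% and 28.6% with 16 pairs. With very highly correlated measures the figure at 52 patients is about 18% to 21%.

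**What the exploratory labels reach.**

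- The label in Statistical analysis is on regressions for factors associated with haemodynamic improvement and clinical outcomes. The example predictors there are baseline characteristics; change in perfusion is not among them.
- The label in Limitations is on multivariable analyses.
- The associative caveat concerns confounding in a single-arm design.

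None of these names the perfusion–recovery correlations, and none deals with chance findings from many tests.

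**After the change.** One pre-named pair tested at 0.05 has a 5% false-positive chance. Keeping every pair with a Bonferroni correction would need 0.05/12 = 0.0042 or 0.05/16 = 0.0031 per test.

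**The case against.** The strongest reply is that choosing the pair, the coefficient and the multiplicity rule for a secondary aim is ordinary analysis-plan content, and a statistical analysis plan may exist unseen. That stands: the absence of a named pair from a journal article is not itself an error. What remains is what the article does state, namely a sentence promising a determination, a two-part haemodynamic definition and a flat 0.05 threshold.

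Second, the aim is not presented as confirmatory. The Introduction uses the verb investigate and places the relationship under secondary endpoints. The secondary objective and the outcome definitions list no correlation, and no power is attached to one. This also stands, so a reader who infers that the protocol plans a confirmatory test here goes further than the text. The overclaim rests on the one Discussion sentence.

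Third, the caveats are real. The findings are called associative, external validation is called for, and the predictor list is open-ended, so a regression of recovery on perfusion change could fall under the exploratory label. These soften the point. They do not address chance findings among many correlations, and the correlations are not named.

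Fourth, the grid is assembled from the article's lists; Statistical analysis sets out no pairwise procedure. The sentence in Data management is generic and should not be read as a declared search for significant pairs.

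Finally, a reader might infer that a cognitive composite is needed to decide the aim. The documents do not support that: no composite appears in the article, and the Discussion justifies the battery by its ability to show domain-specific changes that a global measure may miss.

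**Conclusion.** The point holds as a minor to moderate one about a secondary aim. The Discussion promises a determination that an unranked set of at least 12 to 16 correlations at 0.05 cannot support, and no exploratory label in the article covers those correlations.

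The size is conditional. If any single significant pair were taken as the answer, the false-link chance with no true association would be roughly 25 to 50% for moderately to strongly correlated measures. The outer limits for 12 to 16 pairs are about 18% (very highly correlated) and 56% (16 independent tests). The correlations are assumed, and the any-one-hit rule is a possible reading that the article never states. A reader might therefore take 25 to 50% as the trial's error rate for this aim; the documents do not support that. Even the low end is more than three times the nominal 5% (18/5 = 3.6), which is enough to justify correcting the wording.

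**What to change.** In Statistical analysis, extend the exploratory label to all correlations of perfusion or angiographic measures with neurological or cognitive change. Report each as r with a 95% confidence interval and state how many were examined. In the Discussion, replace the promise to determine an answer with wording for an exploratory association.

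If the sponsor wants a conclusive answer, it should instead name, before analysis, one perfusion measure, one score of its own choice and the 6-month interval as the single deciding correlation at two-sided 0.05, with all others exploratory. If a statistical analysis plan already names such a pair, the article should say so.

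The cost is wording only, with no new data or visits. The downside is that correlations outside a named pair cannot be claimed as confirmed, and with no named pair none can.
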